# Ex-Vivo Study of Heracure Device for Vaginal Intrauterine Cavity Morcellation

Protocol No.: CP-0300

Revision: F

Page 3 of 11

## 1. REVISION HISTORY

| Revision      | ECO#                                                        | Date        | Change Subject                 |
|---------------|-------------------------------------------------------------|-------------|--------------------------------|
| A, B, C, D, E | < Refer to CP-0300 Rev E – Section 1 - "Revision History" > |             |                                |
| F             | 0033                                                        | 17-Nov-2022 | Revisions per PLUS ONE request |

## 2. ACRONYMS, INITIALS, and DEFINITIONS

|     |                        |
|-----|------------------------|
| AE  | Adverse Event          |
| CBC | Complete Blood Count   |
| CRF | Case Report Form       |
| EC  | Ethics Committee       |
| GCP | Good Clinical Practice |
| IFU | Instruction for Use    |
| LDH | Lactate Dehydrogenase  |
| PAP | Papanicolaou           |
| SAE | Serious Adverse Event  |

|                                                                               |             |              |
|-------------------------------------------------------------------------------|-------------|--------------|
| Ex-Vivo Study of Heracure Device for Vaginal Intrauterine Cavity Morcellation |             |              |
| Protocol No.: CP-0300                                                         | Revision: F | Page 4 of 11 |

### 3. STUDY ABSTRACT/SYNOPSIS

|                                  |                                                                                                                                                                                                                                                                                                                                            |
|----------------------------------|--------------------------------------------------------------------------------------------------------------------------------------------------------------------------------------------------------------------------------------------------------------------------------------------------------------------------------------------|
| Protocol Title:           | Ex-Vivo Study of Heracure Device for Vaginal Uterine Intrauterine Cavity Morcellation                                                                                                                                                                                                                                                      |
| Protocol No:              | CP-0300                                                                                                                                                                                                                                                                                                                                    |
| Sponsor:                  | Heracure Medical Ltd.                                                                                                                                                                                                                                                                                                                      |
| Study Objective:          | The purpose of this feasibility EX-VIVO study is to evaluate the safety and efficacy of the device for vaginal intrauterine cavity morcellation (uterine size reduction) after vaginal/laparoscopic hysterectomy                                                                                                                           |
| Study Design:             | Observational Study, Single-arm                                                                                                                                                                                                                                                                                                            |
| Study Device:             | Heracure Device                                                                                                                                                                                                                                                                                                                            |
| Number of Sites           | 1                                                                                                                                                                                                                                                                                                                                          |
| Population                | Participants will be recruited from a list of patients consented for hysterectomy with uterus size $\leq$ 18 weeks. During the procedure, the Heracure System will be used for vaginal uterine size reduction, where the safety & efficacy of the device will be evaluated.                                                                |
| No. of Subjects           | Up to 30                                                                                                                                                                                                                                                                                                                                   |
| Follow Up                 | Not required                                                                                                                                                                                                                                                                                                                               |
| Study Duration            | Up to 12 months                                                                                                                                                                                                                                                                                                                            |
| Procedure:                | EX-VIVO Feasibility Study on Extirpated Uteri
The purpose of this feasibility EX-VIVO study is to evaluate the safety and efficacy of the device for vaginal intrauterine cavity morcellation (uterine size reduction).                                                                                                          |
| Study Endpoints           | Safety – Serious Adverse Device Effects
Procedure Safety will be assessed by recording all the adverse device effects that occur during the treatment with Heracure System.
Adverse Event for the ex-vivo study will be defined as uterine perforation at the end of procedure, assessed by inflating the uterus with saline. |
| Study Secondary Endpoints | Device Success/ Physician satisfaction
Defined as ability to reduce uterus size/circumference, and the time required for performing the morcellation procedure                                                                                                                                                                   |

### 4. INTRODUCTION

#### MORCELLATION OF LARGE UTERI

Minimally invasive surgery is commonly used for hysterectomies because of its many benefits over open surgery. Uterine size is one of the major determining factors in selecting the ultimate hysterectomy surgical approach. A measurement of approximately 12 weeks or less usually allows for a vaginal approach. If the estimate of uterine size is larger than 12 weeks, it is likely that the surgeon will choose an abdominal surgical approach. If the uterine size is estimated above 18 weeks, it is almost certain that an abdominal approach will be selected. The abdominal approach is associated with longer hospital stay and recovery time, greater pain, and greater risk of infection, and minimally invasive approaches are associated with shorter lengths of stay and faster recovery times.

Although small uteri can be removed whole in this approach, larger specimens must be morcellated. Since abdominal morcellation has become controversial recently because of concerns regarding dissemination of occult malignancy and since the current solution of abdominal bag morcellation is cumbersome and time consuming, new techniques that allow surgeons to offer women with large uteri a minimally invasive approach should be investigated and encouraged.

## 5. DEVICE DESCRIPTION

### 5.1 Device Identifications

| Catalogue No. | Description     | Manufacturer                  |
|---------------|-----------------|-------------------------------|
| HERA-RS-2000  | Heracure System | Heracure Medical Ltd., Israel |

Traceability is established through the use of Lot Numbers for each Finished Device lot.

### 5.2 Intended Use:

Heracure System is intended for use in gynecologic and general surgical endoscopic procedures by trained professional professionals in hospital environments and ambulatory surgery centers.

### 5.3 Device Description

Heracure System consists of the following components:

- Heracure Resection Device
- Motor Control Unit and Foot Pedal
- External Vacuum Source Device with Sterile Tubing Sets

The Heracure System features a rotating/oscillating cutting blade for resection of target tissue. The device's cutting blade is controlled by the controller. Distention/Irrigation fluid and resected tissue are transported from Heracure Resection Device to a vacuum canister via sterile disposable tubing-sets protruding from the proximal end of Heracure Resection Device.

[figure not shown]

**Figure 1: Heracure System**

**6. STUDY DESIGN**

The study is designed as an observational study, single-arm study. Any patient who is scheduled for hysterectomy procedure that match the inclusion/exclusion criteria will be offered to give consent.

**7. STUDY OBJECTIVES**

The purpose of this feasibility EX-VIVO study is to evaluate the safety and efficacy of the device for vaginal intrauterine cavity morcellation (uterine size reduction) after vaginal/laparoscopic hysterectomy

**8. STUDY ENDPOINTS****8.1 Primary Endpoints & Success Criteria**

| Primary Endpoint                               | Test Method                                                                                                                                                                                                                                                                              |
|------------------------------------------------|------------------------------------------------------------------------------------------------------------------------------------------------------------------------------------------------------------------------------------------------------------------------------------------|
| Safety – Serious Adverse Device Effects | Procedure Safety will be assessed by recording all the adverse device effects that occur during the treatment with Heracure System.
Adverse Event for the ex-vivo study will be defined as uterine perforation at the end of procedure, assessed by inflating the uterus with saline. |

**8.2 Secondary Endpoints & Success Criteria**

| Secondary Endpoint                                | Test Method                                                                                                                               |
|---------------------------------------------------|-------------------------------------------------------------------------------------------------------------------------------------------|
| Device Success/
Physician Satisfactory | Device Success is defined as ability to reduce uterus size/circumference, and the time required for performing the morcellation procedure |

**9. STUDY INCLUDING/EXCLUSION CRITERIA****9.1 Inclusion Criteria**

- Healthy female aged above 21
- Scheduled for hysterectomy
- Subject has a normal Papanicolaou test (PAP smear)
- Subject signs and dates a written informed consent form (ICF) and indicate an understanding of the study procedures.

**9.2 Exclusion Criteria**

- Subject is pregnant
- Subject is suspected to have endometrial pathology, such as hyperplasia or carcinoma (abnormal Pipelle result or ultrasound screening)
- Subject is suspected to have cervical cancer (abnormal PAP smear result)
- Subject is suspected to have leiomyosarcomas prior to surgery (abnormal signs of rapid growth of lesion, LDH levels or ultrasound screening)
- Subject is suspected to have HIV infection, hepatitis B, CJD, or other sexually transmitted diseases or illness.
- Any other reason for which the individual study subject is not appropriate or suitable for participation
- Subject is unable to give consent

**10. STUDY PROCEDURE/FLOW****10.1 Study Procedure for EX-VIVO Study**

| ASSESSMENT                                                         | SCREENING/
PRE-PROCEDURE | PROCEDURE | DISCHARGE | FOLLOW-UP
VISIT 30 DAYS |
|--------------------------------------------------------------------|-----------------------------|-----------|-----------|----------------------------|
| Inclusion/Exclusion Criteria                                       | X                           |           |           |                            |
| Cervical Screening:
PAP Smear Test                              | X                           |           |           |                            |
| Endometrial biopsy
(Pipelle) - in case of
irregular bleeding | X*                          |           |           |                            |
| Laboratory tests: Lactate
Dehydrogenase (LDH) test              | X*                          |           |           |                            |
| Informed Consent                                                   | X                           |           |           |                            |

- If applicable

**10.2 Study Phases****10.2.1 Screening and Enrollment/Pre-procedure**

10.2.1.1 The physician will allocate appropriate candidates for enrollment based on meeting the general inclusion criteria.

10.2.1.2 If the patient is interested in participating in the study, following a thorough explanation from the physician, the patient will sign an informed consent form.

10.2.1.3 The physician will then verify that the patient complies with the study inclusion/exclusion criteria.

10.2.1.4 Endometrial biopsy (Pipelle) will be used to rule out endometrial pathology, such as hyperplasia or carcinoma. PAP smear test is used to rule out cervical cancer. Lactate Dehydrogenase (LDH) test and the ultrasound screening will be used to rule out patients suspected to have leiomyosarcomas. If cancer is suspected, patient shall be excluded/removed from the study.

**10.2.2 Procedure for Conducting EX-VIVO Study on Extirpated Uteri**

10.2.2.1 The Study will be conducted on whole extirpated uterus.

10.2.2.2 In order to minimize the interference with the hospital routine pathology analysis of uterus, an endometrial biopsy ("Pipelle") will be performed prior to the hysterectomy procedure to enable the data for ruling out endometrial pathology, such as hyperplasia or carcinoma.

10.2.2.3 The purpose of this feasibility EX-VIVO study is to evaluate the safety and efficacy of the device for intrauterine cavity morcellation (e.g., reducing uterine size from the inside of the uterine cavity). During the morcellation procedure, a protective barrier will be wrapped around the uterus.

10.2.2.4 The size of the uterus (e.g., circumference, weight) shall be recorded before and after the morcellation procedure, as well as the total resection time.

10.2.2.5 To assess uterine perforation at the end of procedure, the uterus shall be inflated with saline and observed for leakage.

10.2.2.6 At the end of the procedure, the entire uterus and its resected tissue will be sent to pathology for hospital routine pathology analysis.

## 11. DURATION OF STUDY

Study duration up to 12 months

## 12. RISK ANALYSIS

The risks related to the investigational procedure are mitigated by:

12.1 Inclusion/Exclusion Criteria, which are provided in Section 9 of this protocol.

12.2 Consistent with the current hospital protocol, after completing the testing, all samples will be returned to pathology, where routine pathological analysis will be conducted. In the case that the pathologist on site is identifying an abnormal appearance of the uterine tissue, study will be discontinued, and samples will be sent to pathology, where routine pathological analysis will be conducted.

## 13. MANAGEMENT OF ADVERSE EVENTS

13.1 An adverse event is any undesirable or unintentional event that occurs during the course of the study, considered related to Heracure device. Regardless of severity or relationship to the investigational device, all adverse events occurring during the study must be recorded in the patient's CRF.

13.2 Due to the nature of the current study performed on ex-vivo extirpated uterus (no patient is involved), an adverse event will be defined in the study as uterine perforation at the end of procedure, assessed by inflating the uterus with saline, or any event that leads to interference with the hospital routine pathology analysis of the uterus post procedure.

## 14. ETHICS

### 14.1 Declaration of Helsinki

The study will be conducted according to the guidelines established in the Declaration of Helsinki, ICH E-6 GCP Guidelines and ISO 14155 requirements.

### 14.2 Patient Withdrawal from the Study

14.2.1 Reasons for removing a patient from the ex-vivo study

- Patients who express a desire to withdraw from the study.
- Any medical condition that, in the opinion of the investigator, warrants discontinuation from the study.
- In the case that the pathologist on site is identifying an abnormal appearance of the uterine tissue, study will be discontinued, and samples will be sent to pathology.

14.2.2 The investigator must record the reason for any patient withdrawal from the study.

14.2.3 Patients withdrawn for any reason will be replaced by patients who meet the inclusion and exclusion criteria at the discretion of the principal investigator.

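### Section 14.2.3 lets a uterus already treated with the device be substituted without a perforation result, so the primary safety rate is open to selective loss

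*Protocol*

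**What the plan says.** **Replacement.** Protocol section 14.2.3: "Patients withdrawn for any reason will be replaced by patients who meet the inclusion and exclusion criteria at the discretion of the principal investigator". No point in time is given, such as first activation of the device, after which replacement no longer applies.

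**Reasons for withdrawal.** Section 14.2.1 lists three: the patient's wish; "Any medical condition that, in the opinion of the investigator, warrants discontinuation from the study"; and the on-site pathologist "identifying an abnormal appearance of the uterine tissue, study will be discontinued, and samples will be sent to pathology". Because the third stands in a list of reasons for removing a patient, I read it as ending that specimen's part in the study and not the whole trial. Section 14.2.2 adds: "The investigator must record the reason for any patient withdrawal from the study".

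**Primary endpoint.** Section 8.1: "Procedure Safety will be assessed by recording all the adverse device effects that occur during the treatment with Heracure System". It continues: "Adverse Event for the ex-vivo study will be defined as uterine perforation at the end of procedure, assessed by inflating the uterus with saline". Section 10.2.2.5 gives the test: "To assess uterine perforation at the end of procedure, the uterus shall be inflated with saline and observed for leakage".

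**Design and size.** Section 6: "The study is designed as an observational study, single-arm study". The synopsis caps enrolment at 30. Section 20 promises descriptive statistics only.

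**The concern.** In a single-arm study with a descriptive analysis, the perforation count and its denominator are the whole primary result. No comparator would share, and so partly cancel, a selection effect.

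The rule on replacement governs conduct, and the protocol sets it without limit. At least one listed reason concerns the extirpated uterus itself. It can arise only after surgery, and nothing confines it to the time before morcellation starts. On that path the specimen goes to pathology, and no saline test is mentioned. Section 14.2.2 secures the reason for withdrawal but not the perforation status.

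A treated uterus can thus have no observed primary outcome while another fills its place. If whether a uterus is stopped early has anything to do with how it tolerated the device, the uteri that complete the procedure are a selected group and their perforation rate does not describe the device's use.

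**Working it through.** The protocol gives no expected perforation rate, withdrawal rate, power or precision target, so there is no stated figure to reproduce. The check has three steps.

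**1. Can a treated uterus reach replacement without a result?**

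- Sections 8.1 and 10.2.2.5 place the perforation test at the end of the procedure only.
- Section 14.2.1 allows withdrawal for abnormal tissue appearance, with no limit to the time before device use. Section 12.2 repeats this discontinuation, also with no test stated.
- Section 14.2.3 then permits replacement.

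The three together allow it. How often it would happen cannot be derived from the protocol.

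**2. Direction and size of the bias.** Let *p* be the true perforation rate, *a* the share of perforated treated uteri that are withdrawn and substituted, and *b* the same share among non-perforated treated uteri. The expected rate among retained uteri is

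r = p(1 − a) / [p(1 − a) + (1 − p)(1 − b)].

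All values of *p*, *a* and *b* below are assumptions.

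| p | a | b | Calculation | r |
|---|---|---|---|---|
| 10% | 10% | 10% | 0.090 / (0.090 + 0.810) | 10.0% |
| 10% | 20% | 5% | 0.080 / (0.080 + 0.855) | 8.6% |
| 10% | 30% | 5% | 0.070 / (0.070 + 0.855) | 7.6% |
| 10% | 50% | 5% | 0.050 / (0.050 + 0.855) | 5.5% |
| 10% | 5% | 20% | 0.095 / (0.095 + 0.720) | 11.7% |
| 5% | 30% | 5% | 0.035 / (0.035 + 0.9025) | 3.7% |
| 20% | 30% | 5% | 0.140 / (0.140 + 0.760) | 15.6% |

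Equal withdrawal leaves the rate unchanged. Its direction otherwise depends on which group is withdrawn more often.

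**3. What single uteri do to the reported figure.** Suppose 30 uteri are retained with no perforation, and *k* further treated uteri, all perforated, were substituted. Exact (Clopper-Pearson) 95% intervals:

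| k | Substituted uteri left out | All treated uteri kept |
|---|---|---|
| 1 | 0/30 = 0% (0 to 11.6%) | 1/31 = 3.2% (0.1 to 16.7%) |
| 2 | 0/30 = 0% (0 to 11.6%) | 2/32 = 6.3% (0.8 to 20.8%) |
| 3 | 0/30 = 0% (0 to 11.6%) | 3/33 = 9.1% (1.9 to 24.3%) |

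Each lost perforation moves the estimate by about 3 percentage points. If a substituted uterus was never tested, its status is unknown. With *k* = 1 the data then support only a range, from 0/31 = 0% to 1/31 = 3.2%.

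**The case against.** The strongest reply is that replacing a patient is not deleting her data. A reader might infer from 14.2.3 that a perforated uterus can simply be struck from the count. The protocol does not say so. Section 8.1 assesses safety by recording all adverse device effects during treatment, section 13.1 requires all adverse events in the CRF, and section 14.2.2 requires the withdrawal reason. A perforation already found should be on record, and an analysis of all treated uteri can include it. The analysis population may also be defined in a statistical analysis plan that is not shown. This stands, and it rules out saying that no later analysis could repair the result. It does not reach a uterus stopped before the saline test, because neither the CRF nor an analysis plan can supply an outcome that was never observed.

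A reader might also infer that the rule necessarily lowers the perforation rate. It does not. Perforation is not a listed withdrawal reason, the protocol gives no evidence that abnormal tissue perforates more readily, and the formal determination comes only at the end. A large downward bias appears only if withdrawal is assumed to fall mainly on perforated uteri.

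The investigator's discretion in 14.2.3 might be taken as control over who is withdrawn. As worded it attaches to replacement. For withdrawal, investigator opinion enters only through the medical-condition reason in 14.2.1. Deleting the discretion phrase would keep no uterus in the count.

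Finally, this is a feasibility study with no hypothesis test and no numerical success threshold that a substitution could flip. That is fair, and it limits the severity.

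**Conclusion.** The point holds as a badly set conduct rule. Section 14.2.3 has no cut-off at device use and nothing ties a treated uterus to the primary count. Because the test is done only at the end of the procedure, a treated uterus can be substituted with its primary outcome unobserved.

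The consequence is exposure to selective loss in either direction, not a demonstrated downward bias. At the cap of 30, one lost perforation is worth about 3 percentage points. Under the assumed withdrawal patterns, a true rate of 10% would be reported as anything from 5.5% to 11.7%, and as 10.0% when withdrawal is unrelated to perforation. These figures rest on assumed rates; the protocol gives none.

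The documents do not support the stronger readings that recorded perforations are discarded or that the damage is beyond repair in every case. It is beyond repair only where the test was not done. Severity is moderate.

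**What to change.** Rewrite 14.2.3 in one of two ways:

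- allow substitution only for patients withdrawn before the device is activated on the uterus; or
- state that any replacement after activation is additional to the treated uterus and does not take its place.

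Under either wording, add that every uterus on which the device was activated stays in the primary safety denominator. Each is reported as perforated, not perforated or not assessed, with the withdrawal reason. Where a patient refuses use of her data, report the count and the reason only. If the second wording is chosen, say whether the cap of 30 includes the replaced uteri, since the number treated could otherwise exceed it.

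The cost is one paragraph and no new procedure. The reported perforation rate may come out slightly less favourable, and any unassessed uteri will be visible.
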